# PROTOCOL SYNOPSIS

| **Study Drug** | Apatinib plus Capecitabine |
| --- | --- |
| **Study Title** | A Phase II Study to Evaluate the Efficacy and Safety of Apatinib in Combination with Capecitabine in Patients with Recurrent/Metastatic Nasopharyngeal Carcinoma Who Failed Platinum-based Therapies |
| **Investigator** | [name]; [name] |
| **Protocol Version** | 2.2 |
| **Protocol Date** | October 29, 2018 |
| **Study Design** | A non-randomized, open-label, single-arm exploratory study |
| **Study Properties** | A clinical study initiated by the investigator |
| **Study Subjects** | Patients with recurrent/metastatic advanced nasopharyngeal carcinoma (NPC) who failed platinum-based therapies |
| **Study Objective** | To evaluate the efficacy and safety of apatinib combined with capecitabine in the treatment of patients with recurrent/metastatic advanced NPC who failed platinum-based therapies |
| **Study Sample Size** | This study is a superiority trial using Simon's two-stage design to estimate the sample size. Alpha is 0.05, Beta is 0.2, and the testing power is 0.8. According to literature, the ORR of capecitabine monotherapy is 24.2%, assuming that the ORR of the combination of apatinib and capecitabine increases by 15%, i.e., ORR = 39.2%, and the drop-out rate of 10%, at least 64 cases are needed. In the first stage, 31 cases will be enrolled, when the number of effective cases is less than 8, it is considered that the efficacy of the drug combination is not better than the monotherapy, and the trial will be terminated. Otherwise, continue to the second stage of enrollment. |
| **Subject Eligibility Criteria: Inclusion Criteria** | Patients to be included in this study must meet all of the following inclusion criteria:  1) Patients with histologically proven recurrent and/or metastatic NPC;  Patients with recurrent and/or metastatic NPC shall meet any of the following items: 1. Recurrence after radiotherapy; 2. Metastasis  2) Patients who have failed the platinum-based therapy and received at least first-line platinum-containing chemotherapy;  3) Male or female patients: aged 18-70 y/o;  4) ECOG Performance Status score: 0-2;  5) The estimated survival is ≥ 3 months;  6) Patients not receiving chemotherapy or radiotherapy 4 weeks before the inclusion;  7) With at least one measurable lesion according to the RECIST criteria (the size measured with MRI or spiral CT scan is ≥ 10 mm and the measurable lesion has not received any radiotherapy);  8) Patients whose major organs function well, i.e., to meet the following requirements 1 week before the inclusion:  a. Routine blood test:  i. Hemoglobin > 80 g/L (no blood transfusion within 14 days);  ii. Neutrophil count > 1.5 × 10^9^/L;  iii. Blood platelet count > 80 × 10^9^/L;  b. Biochemical examination:  i. Total bilirubin ≤ 1.5 × ULN (upper limit of normal);  ii. ALT or AST ≤ 2.5 × ULN (upper limit of normal);  iii. Creatinine < 2.0 × ULN, endogenous creatinine clearance rate > 50 ml/min (Cockcroft-Gault Equation);  9) Females of child-bearing age must undergo a pregnancy test (serum or urine) 7 days before the inclusion, with a negative result and a willingness to take reliable contraceptive methods during the trial;  10) Subjects voluntarily participate in the study, sign the Informed Consent form, and are well compliant and cooperative in follow-ups. |
| **Subject Eligibility Criteria: Exclusion Criteria** | Patients that meet any of the following items shall not be included in this study:  1) Patients who are allergic to any of the drugs in this study;  2) Pregnant or lactating females;  3) Patients who have participated in clinical trials of other drugs within 4 weeks before this study;  4) Patients who have received radiology for twice or more times;  5) Patients who have received the treatment with VEGFR small-molecule tyrosine kinase inhibitors (such as famotidine, sorafenib, sunitinib, regofinib, anlotinib, fruquintinib);  6) Patients whose MRI images show tumors have invaded important blood vessels (such asthe surrounding internal carotid artery/vein); or patients who are highly likely to experience fatal hemorrhage due to the potential impact of tumors on important vessels, as judged by the investigators;  7) Patients with severe hemorrhage history and undergoing any hemorrhage event of Grade 3 or above in CTCAE (Version 4.0) within 4 weeks before the inclusion;  8) Hypertensive patients who cannot be well controlled by a single anti-hypertensive drug (systolic blood pressure > 140 mmHg, diastolic blood pressure > 90 mmHg); cardiovascular disease with clinical significance (e.g. active), such as cerebrovascular accident (≤ 6 months before randomization), myocardial infarction (≤ 6 months before randomization), unstable angina pectoris, congestive heart failure with the NYHA classification of Class II or above, or severe arrhythmias that cannot be controlled with drugs or have a potential impact on the trial treatment;  9) Patients with active ulcer, intestinal perforation and intestinal obstruction;  10) Patients with a digestive tract perforation history 28 days before the selection;  11) With multiple factors affecting oral administration and absorption of drugs (such as being unable to swallow, after gastrointestinal resection, chronic diarrhea and intestinal obstruction);  12) Patients with abnormal coagulation and bleeding tendency (14 days before signing the Informed Consent form, the following conditions must be met: INR is within a normal range without the use of anticoagulants); patients treated with anticoagulants or Vitamin K antagonists such as warfarin and heparin or similar drugs; under the premise that the INR of the prothrombin time is ≤ 1.5, small doses of warfarin (1 mg, oral administration, once a day) or small doses of aspirin (the daily dosage shall not exceed 100 mg) are permitted for preventive purposes;  13) Patients suffering from arterial/venous thrombosis events within 6 months before the screening, such as cerebrovascular accidents (including transient ischemic attacks), deep vein thrombosis (except for patients who had venous thrombosis caused by intravenous catheterization due to previous chemotherapy and are judged to have recovered by the investigators) and pulmonary embolism;  14) Patients with renal insufficiency: Urinary routine proteinuria > 2+ and the urinary protein quantification of 24 hours is confirmed to be > 1.0 g;  15) Patients undergoing major surgery within 28 days;  16) Patients who have received the treatment with potent CYP3A4 inhibitors 1 week before the inclusion or received the treatment with potent CYP3A4 inductive agents within 2 weeks before participating in this study;  17) Patients with chronic unhealed wounds or incompletely healed fractures;  18) Patients with symptomatic brain metastasis (confirmed or suspected);  19) Patients with severe or uncontrolled infection;  20) Patients with a history of psychotropic substance abuse and unable to quit or with mental disorder history;  21) Patients with a history of immunodeficiency diseases, including HIV-positive, or with other acquired or congenital immunodeficiency diseases, or with organ transplant history;  22) Patients with past or present objective evidence for pulmonary fibrosis, interstitial pneumonia, pneumoconiosis, radioactive pneumonia, drug-related pneumonia, severe pulmonary function impairment;  23) Patients with a history of other malignant tumors in the past 5 years, except for cured skin basal cell carcinoma, cervical carcinoma in situ and superficial bladder cancer;  24) Concomitant diseases that seriously endanger patients' safety or affect patients' completion of this study, as judged by the investigators. |
| **Drug Dosing and Administration Regimen** | Apatinib Mesylate Tablets 500 mg, po, qd, q4w, plus Capecitabine tablets 1000 mg/m^2^, po, bid, d1-14, q3w (take the medicine at the same time every day as possible);  A treatment cycle lasts 3 weeks, and the combined medication will be continued until the occurrence of toxicity intolerance, disease progression, or death, or patients refuse to continue participating in this clinical study, or the investigators determine that the medication must be terminated. |
| **Study Efficacy Evaluation** | **Intent-to-Treat (ITT) Population**: The ITT population is defined as all subjects who are enrolled.  **Per Protocol (PP) Population**: The per protocol population (PP) defines as a subset of the subjects who meet all of the trial criteria and are compliant with the protocol and absence of any major protocol violations.  The efficacy is assessed by imaging examinations and the RECIST 1.1 criteria will be employed:  **Primary efficacy indicators:** Objective response rate (ORR) of tumor  **Secondary efficacy indicators:**   1. Disease control rate (DCR) 2. Duration of response (DoR) 3. Patient's progression-free survival (PFS) 4. Overall survival (OS)   5) Safety and tolerance of the regimen |
| **Study Safety Evaluation** | All the patients that have received the treatment with the test drugs for at least one cycle, and have safety records will be taken as an effective population for safety analysis. The abnormal values of patients' physical examination results, vital signs, adverse events and laboratory examinations will be summarized. Adverse events will be reported and classified according to the Common Terminology Criteria for Adverse Events (CTCAE) Version 4.0 of the NCI. |
| **Study Statistical Methods** | Efficacy evaluation:  The 95%CI of ORR and DCR are calculated based on the Clopper-Pearson exact method.  The Kaplan-Meier method is used to estimate the median DOR, PFS and OS, and survival curves will be created.  Safety evaluation:  Safety evaluation is mainly based on descriptive statistical analyses and lists the adverse events and adverse reactions occurring in this trial (adverse reactions are defined as "adverse events that are 'definitely related/probably related/likely related to' the test drugs"). The laboratory examination results describe circumstances that are normal before the test but abnormal after the treatment, as well as their relationships with the test drugs when an abnormal change occurs. |

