12) Patients suffering from arterial/venous thrombosis events within 6 months before the screening, such as cerebrovascular accidents (including transient ischemic attacks), deep vein thrombosis (except for patients who had venous thrombosis caused by intravenous catheterization due to previous chemotherapy and are judged to have recovered by the investigators) and pulmonary embolism;

13) Patients with renal insufficiency: Urinary routine proteinuria > 2+ and the urinary protein quantification of 24 hours is confirmed to be > 1.0 g;

14) Patients with symptomatic brain metastasis (confirmed or suspected);

15) Patients with a history of other malignant tumors in the past 5 years, except for cured skin basal cell carcinoma, cervical carcinoma in situ and superficial bladder cancer;

16) Concomitant diseases that seriously endanger patients' safety or affect patients' completion of this study, as judged by the investigators.

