### 3.4.3. Removal Criteria

Subjects who have been included but subject to any of the following circumstances should be removed from the study:

1) The subject is found to be mistakenly included in the trial because he/she did not meet the inclusion/exclusion criteria;

2) The subject fails to follow the drug dosage, administration method and course of treatment specified in this study protocol (but he/she should be observed for drug-related AEs).

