**2) The following screening procedures must be completed within 7 days before the study drug treatment starts:**

• ECOG scoring;

• Vital signs: Heart rate, respiratory frequency, body temperature, blood pressure;

• Physical examination: Head and face, skin system, lymph nodes, eyes, ear, nose and throat, mouth, respiratory system, cardiovascular system, abdomen, genitourinary system, musculoskeletal system, nervous system and mental state;

• Blood routine: Hemoglobin, red blood cells, leukocytes, neutrophils, lymphocytes, platelets;

• Urine routine: Urine protein, urine sugar, urine occult blood (urine red blood cell, white blood cell), urine pH and urine ketone bodies;

If the semi-quantitative test shows protein ≥ 2+, the 24-hour urine protein quantitative test should be performed. All patients included must have a 24-hour urine protein level of less than 1g.

• Fecal routine: Feces OB test;

• Blood biochemistry test: Total bilirubin, direct bilirubin, indirect bilirubin, ALT, AST, AKP, r-GT, total protein, albumin, urea nitrogen, creatinine, uric acid, blood glucose, triglyceride, cholesterol, blood lipase, blood amylase, potassium, sodium, chlorine, calcium and phosphorus;

• Coagulation function test: PT, APTT, TT, Fbg and INR;

• EB virus detection (by PCR);

• Blood sample: If a patient is to be included certainly, his/her peripheral blood should be collected to determine serum VEGF-A/C and VEGFR-2 levels, and VEGF and VEGFR2 gene polymorphisms;

• ECG: 12-lead ECG examination. QT, QTc and P-R intervals will be observed carefully, and ECG will be performed for three consecutive times to identify abnormalities (with a 5-minute interval each time and the QTc interval marked);

• Myocardial enzyme spectrum examination: Patients will only receive one examination within 7 days before the inclusion, no examination is needed in the future, and supplementary examination is only performed when the ECG is abnormal;

• Pregnancy test (for female patients of child-bearing age);

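### Eight synopsis exclusions are missing from section 3.4.2, and the proteinuria exclusion does not agree with the screening rule in 3.8.1

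*Protocol*

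**What the plan says.** The synopsis gives its exclusions as a binding list: meeting any one of them bars entry. It runs to item 24, "24) Concomitant diseases that seriously endanger" and so on. Section 3.4.2 of the same protocol version ends on the same topic, but there it is item 16: "16) Concomitant diseases that seriously endanger". Among the synopsis items with no match in the body are item 15, "Patients undergoing major surgery within 28 days", and item 17, "Patients with chronic unhealed wounds or incompletely healed fractures".

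On proteinuria, synopsis item 14 and item 13 of section 3.4.2 use the same words: "Urinary routine proteinuria > 2+ and the urinary protein quantification of 24 hours is confirmed to be > 1.0 g". The screening procedures in section 3.8.1 call for the 24-hour test at 2+ or above and then state: "All patients included must have a 24-hour urine protein level of less than 1g".

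Two later provisions depend on eligibility. Section 3.4.3 removes from the study any subject "mistakenly included in the trial because he/she did not meet the inclusion/exclusion criteria". The synopsis restricts the per-protocol population to subjects who satisfy every trial criterion.

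**The concern.** A synopsis may fairly shorten the body of a protocol. Here the body, which sites would normally work from, is the shorter text, and nothing says which list governs. A site using 3.4.2 can enrol a patient whom the synopsis bars, and another site or a monitor using the synopsis would call that patient ineligible.

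Some of the missing items bear on safety by the protocol's own account. The notes to Appendix 3 warn that drugs acting on blood vessels can impair wound healing and recommend a pause before biopsy, yet 3.4.2 has no explicit bar on unhealed wounds or recent major surgery.

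The same ambiguity carries into 3.4.3 and the per-protocol definition. Both turn on whether a patient met the criteria, and with two lists that question can have two answers.

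**Working it through.** No power or error-rate formula applies. The check sets the two lists side by side and then compares the proteinuria rules.

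**Step 1: match the lists by topic.**

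| Synopsis items | Section 3.4.2 items |
| --- | --- |
| 2 to 14 | 1 to 13 |
| 18 | 14 |
| 23 | 15 |
| 24 | 16 |
| 1, 15, 16, 17, 19, 20, 21, 22 | none |

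Matched items: 13 + 1 + 1 + 1 = 16. Unmatched: 24 − 16 = 8, and 8/24 is one third of the synopsis list. Every body item has a synopsis counterpart, so the body list is nested within the synopsis list.

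The match is by topic, not word for word. Synopsis item 4 and body item 3 differ in one term (radiology against radiotherapy), and synopsis item 5 and body item 4 differ in one example drug (fruquintinib against furosemide).

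The body numbering has no gap. Item 13 on proteinuria is followed directly by "14) Patients with symptomatic brain metastasis (confirmed or suspected", which is item 18 in the synopsis. The intervening synopsis items 15 to 17 are simply not there.

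**Step 2: the eight unmatched items, and whether body item 16 reaches them.** Body item 16 concerns concomitant diseases that the investigator judges to endanger the patient seriously or to affect completion of the study.

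| Synopsis item | Topic | Reached by body item 16? |
| --- | --- | --- |
| 1 | Allergy to a study drug | Not plainly |
| 15 | Recent major surgery | Not plainly |
| 16 | Strong CYP3A4 inhibitors or inducers | Not plainly |
| 17 | Unhealed wounds or fractures | Perhaps, by judgement |
| 19 | Severe infection | Plausibly, by judgement |
| 20 | Substance abuse or mental disorder | At most by judgement |
| 21 | Immunodeficiency, HIV, transplant | Plausibly, by judgement |
| 22 | Lung fibrosis, pneumonitis, severe lung impairment | Plausibly, by judgement |

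For at least three items the catch-all gives no clear cover. For the rest it replaces a fixed bar with discretion.

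**Step 3: compare the proteinuria rules.** The exclusion item needs both conditions: dipstick above 2+ and more than 1.0 g in 24 hours. Section 3.8.1 tests at 2+ or above and requires less than 1 g.

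| Dipstick | 24-hour protein | Exclusion item (both lists) | Section 3.8.1 |
| --- | --- | --- | --- |
| exactly 2+ | below 1 g | not excluded | passes |
| exactly 2+ | 1.5 g | not excluded | fails |
| above 2+ | exactly 1.0 g | not excluded | fails |
| above 2+ | 1.5 g | excluded | fails |

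The rules disagree in the second and third rows. The disagreement lies between the exclusion item and 3.8.1; on this item the two exclusion lists are identical.

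**Step 4: trace the effect on the analysis sets.**

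- Intention-to-treat (synopsis): all enrolled subjects. No reference to eligibility.
- Full analysis set (3.11.3): all included patients with at least one use of the drug. No reference to eligibility.
- Per-protocol (synopsis): must meet all trial criteria, so it depends on the list.
- Per-protocol set (3.11.3): conformity with the protocol, compliance, no prohibited drugs and completed case reports. It depends on the list only through conformity.
- Removal (3.4.3): depends on the list.

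**The case against.** The strongest reply is that nothing here is truly opposed. The body list sits inside the synopsis list, so a reader who applies the whole protocol applies all 24 exclusions. The 3.8.1 rule can likewise be read as an added requirement, with the stricter rule deciding wherever the two differ. The catch-all would stop several of the eight conditions in practice. On this view the fault is an omission to be tidied.

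Part of that stands. Both sets of rules can be obeyed together, and the gap with no clear cover at all is smaller than eight items. But the protocol never says the lists are cumulative, and a site that follows section 3.4.2 in good faith meets no explicit bar on allergy, recent surgery or CYP3A4 drugs. The omission therefore changes who can be enrolled.

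Three stronger readings are tempting, and the documents do not support them.

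- A reader might infer that the choice of list shifts the primary response rate by changing its denominator. Neither the intention-to-treat nor the full analysis set refers to eligibility, and 3.4.3 speaks of removal from the study without saying that the subject leaves either set.
- A reader might infer that the first-stage decision is exposed. That rule counts responders (stop at 7 or fewer of 31), and removing a non-responder leaves the count unchanged.
- A reader might infer that eligibility would be settled once responses are known. Nothing in the text says so, and most of the eight items can be recorded before treatment.

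Nor does the wound-healing rationale extend to all eight: no section ties substance abuse, mental disorder or HIV to the risks of an antiangiogenic drug.

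**Conclusion.** The point holds as an inconsistency in eligibility. Eight of the 24 synopsis exclusions are absent from section 3.4.2 and are covered there at most in part. As a separate matter, the proteinuria exclusion shared by both lists does not agree with section 3.8.1.

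The consequences are uneven enrolment on criteria that include safety-related ones, and an ambiguous basis for removal under 3.4.3 and for the per-protocol set. The intention-to-treat and full analysis sets as defined are not affected.

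The counts of 24, 16 and 8 are exact and rest on matching by topic. How many patients would be affected cannot be estimated, because the protocol gives no frequency for any of these conditions. The conclusion assumes only that sites may work from either list, which the protocol does not rule out. It takes no position on which criteria or which proteinuria threshold is clinically right.

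**What to change.** Issue one numbered exclusion list and use it verbatim in the synopsis and in section 3.4.2. For each of synopsis items 1, 15, 16, 17, 19, 20, 21 and 22, the sponsor should decide deliberately whether it is in or out, and show the same decision in both places.

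Reconcile the proteinuria exclusion (synopsis item 14, section 3.4.2 item 13) with section 3.8.1, so that one rule states when the 24-hour test is done and which result bars entry.

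Refer to that single list by number in the removal rule of 3.4.3 and in one per-protocol definition used in both the synopsis and 3.11.3.

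The cost is protocol amendment wording, with no extra patients or procedures.

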**3.9.4.3. Judgment of The Relationship between AEs and The Study Drug**

Possible relationships between AE and the study drug will be evaluated as " definitely related, probably related, possibly related, unlikely relatedt and not related" using the five-tier classification method (see the table below). AEs with a relationship of the first three tiers are judged to be related to the study drug. When calculating the incidence of adverse reactions, the total number of patients in the first three tiers should be taken as the numerator, and the total number of all subjects participating in safety evaluation should be taken as the denominator.

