**Criteria for judging the relationship between AEs and the study drug**

| Criteria | Definitely related | Probably related | Possibly related | Unlikely related | Not related |
| --- | --- | --- | --- | --- | --- |
| The time sequence is reasonable | Yes | Yes | Yes | Yes | No |
| The drug reaction type is known | Yes | Yes | Yes | No | No |
| The removal cause can be improved | Yes | Yes | Yes or no | Yes or no | No |
| It will occur again upon next medication | Yes | ? | ? | ? | No |
| The reaction may have another explanation | No | No | No | Yes | Yes |

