### 3.11.3. Statistical analysis Data Set

Full analysis set: It covers all patients included in the study who have used the drug at least once for efficacy analysis based on the intention-to-treat (ITT) principle. For the case data for which the entire treatment process cannot be observed, the last observation data should be carried forward to the final outcome of the trial.

Per-protocol set: It covers all patients who conform to the study protocol, have good compliance, have not taken any prohibited drugs during the study period and complete the case reports as required. No imputation will be made on the missing data. FAS and PPS are statistically analyzed for the efficacy of the drug.

Safety analysis set: It covers all patients included in the study who have used the study drug at least once, and have safety records after medication. This dataset is used for safety analysis.

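### The safety population is defined two ways (one full cycle in the synopsis, one dose in section 3.11.3), and the causality grid leaves some adverse events without a class, so the adverse-reaction rate is not fixed.

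*Protocol*

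**What the plan says.** The protocol defines the safety population twice. The synopsis, under Study Safety Evaluation, takes "All the patients that have received the treatment with the test drugs for at least one cycle", on condition that safety records exist for them. Its dosing entry says that "A treatment cycle lasts 3 weeks". Section 3.11.3 defines the safety analysis set differently: "It covers all patients included in the study who have used the study drug at least once, and have safety records after medication". No statement ranks one definition above the other.

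Section 3.9.4.3 then defines the incidence of adverse reactions. On causality, "AEs with a relationship of the first three tiers are judged to be related to the study drug". For the rate, "the total number of patients in the first three tiers should be taken as the numerator". Everyone in the safety evaluation forms the base of that rate. The safety population is therefore the denominator, and the causality grid in the same section decides the numerator.

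The grid has five criteria and five classes, running from *definitely related* to *not related*. Its last row reads "The reaction may have another explanation | No | No | No | Yes | Yes". The row asking whether the reaction type is known has the opposite entries: yes for the three related classes, no for the other two.

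**The concern.** Safety is part of the study objective and is listed among the secondary objectives (sections 2 and 2.2). In a single-arm trial of about 64 patients, one or two severe events more or less change the safety picture.

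On the denominator, the protocol itself foresees stopping inside cycle 1. Section 3.7.1 has permanent discontinuation for grade 4 hypertension, section 3.7.5 has immediate discontinuation for massive gastrointestinal bleeding, and section 3.7.4 places rash at about one week. If the synopsis definition were applied, a patient who stopped on day 10 for such an event would not be in the safety analysis.

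On the numerator, many events in advanced nasopharyngeal carcinoma have both a drug explanation and a tumour explanation; bleeding is an obvious example. If the grid has no class for such an event, each investigator must choose which cell to ignore. The adverse-reaction rate then depends on an unwritten habit.

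**Working it through.** **1. The number of patients.** Section 3.3 plans 64. That figure is not in dispute. An exact Simon search with response rates 0.242 and 0.392, one-sided alpha 0.05 and power 0.80 gives a minimax design that stops at 7 or fewer of 31 and rejects above 19 of 58 (alpha 0.0495, power 0.8002). Then 58 × 1.1 = 63.8, rounded to 64. Below, 64 serves only as an illustrative number of dosed patients.

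**2. What the one-cycle rule does to a rate.** Let N be the patients dosed, e those who stop before completing cycle 1, p_e their reaction rate and p_l the rate in the others.

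- One-dose rate = [e·p_e + (N − e)·p_l] / N
- One-cycle rate = p_l
- One-cycle minus one-dose = (e/N)·(p_l − p_e)

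The sign depends only on whether early stoppers react more or less often than the rest. The protocol gives no early-stopping rate, so e is assumed to be 3 to 10, p_l to be 50% and p_e to be 10% to 100%.

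| e | p_e | One-dose rate | One-cycle rate | Difference (points) |
|---|---|---|---|---|
| 6 | 100% | (6 + 29)/64 = 54.7% | 29/58 = 50.0% | −4.7 |
| 6 | 50% | (3 + 29)/64 = 50.0% | 50.0% | 0 |
| 6 | 10% | (0.6 + 29)/64 = 46.25% | 50.0% | +3.75 |
| 10 | 100% | (10 + 27)/64 = 57.81% | 27/54 = 50.0% | −7.81 |
| 10 | 10% | (1 + 27)/64 = 43.75% | 50.0% | +6.25 |

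**3. Rarer events.** Suppose 6 patients stop early.

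- With 3 events among them and 2 later, the rates are 5/64 = 7.8% and 2/58 = 3.4%.
- With no early events and 3 later, they are 3/64 = 4.7% and 3/58 = 5.2%.
- As a deliberately adverse case, take 2 fatal bleeds in cycle 1, no later bleed and no other early stopper. One dose gives 2/64 = 3.1% (Clopper-Pearson 95% CI 0.4% to 10.8%). One cycle gives 0/62 = 0% (upper limit 5.8%).

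**4. The causality grid.** Two rows settle the matter:

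| Class | Type known | Other explanation |
|---|---|---|
| Definitely | Yes | No |
| Probably | Yes | No |
| Possibly | Yes | No |
| Unlikely | No | Yes |
| Not related | No | Yes |

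In every column the two answers are opposite. An event with the same answer to both therefore fits no column, whatever the other rows say. Five yes/no criteria give 2^5 = 32 patterns, of which 16 have reasonable timing.

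- Of those 16, 4 have a known type and another explanation, and 4 have an unknown type and no other explanation. These 8 fit no class.
- The other 8 fit at least one class when the question mark and the yes-or-no entries are read as either answer.
- Of the 16 with unreasonable timing, 15 fit no class, because *not related* requires one exact pattern. In total, 8 + 15 = 23 of 32 fit none. The 15 matter less, since the timing already speaks against the drug.

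**The case against.** A reader might infer that both defects bias adverse-reaction rates downward. The protocol does not support that as a general statement.

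- **Safety set.** Any effect arises only if the synopsis wording is used; section 3.11.3 does not have the problem and says its set is the one for safety analysis. Even under the synopsis rule, excluded patients leave the numerator and the denominator together, so the direction depends on why they stopped. This stands.
- **Grid.** One might suppose that a known reaction with another explanation would end up as *unlikely related*. Nothing says so. That class requires an unknown type, so it breaks one cell, and *possibly related* also breaks one. What can be shown is an undefined class, not a direction. This also stands.
- **Loss of events.** One might infer that such events vanish from the record. They do not. Section 3.9.4.2 has all adverse events recorded, section 3.9.5.4 has serious events reported from consent to 30 days after the last medication, and section 3.11.4 lists adverse events as well as adverse reactions. The grid does not touch all-cause counts. Recording does not, however, settle who enters the safety population or what is counted as a reaction.
- **Sunitinib deaths.** The two fatal haemorrhages cited in section 1.4 were in patients with carotid sheath invasion, and section 3.4.2 excludes invasion of important vessels. They do not forecast cycle 1 bleeding here.

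One could also read the synopsis as meaning patients who entered a cycle, which would remove the conflict. But being treated for at least one cycle, with a cycle set at 3 weeks, is most naturally a duration. Finally, safety is secondary and descriptive, and neither defect affects the response-rate test, the sample size or the stopping rule.

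**Conclusion.** Two defects hold as written. First, the synopsis and section 3.11.3 give incompatible safety populations. If the synopsis rule were applied, toxicity would be understated when early stopping is due to toxicity. Under the assumptions shown (64 dosed, 3 to 10 early stoppers, 50% in the rest, 10% to 100% in the early stoppers), the one-cycle rate runs from 7.81 points too low to 6.25 points too high. The 2/64 against 0/62 comparison is arithmetically right but is a hypothetical worst case.

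Second, 8 of the 16 causality patterns with reasonable timing have no class, so the adverse-reaction numerator is undefined for them. The rate is understated if those events are left out of the first three tiers. The count is of patterns, not events; the protocol gives no basis for saying how many events would be affected.

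**What to change.** 1. In the synopsis, define the safety population as all patients who took at least one dose and have safety records after it, as in section 3.11.3.
2. In the grid, set the *possibly related* entry for another explanation to yes or no. In the known-type row, let *possibly related* also take an unknown type when there is no other explanation, and keep *unlikely related* for an unknown type with another explanation. Add a footnote that classes are tried from left to right and the first that fits applies. The 16 patterns with reasonable timing then divide into 1 definitely, 1 probably, 2 + 4 + 4 = 10 possibly and 4 unlikely, which sums to 16. Another allocation would also serve, provided each pattern has exactly one class.
3. While editing, align the name of the third related tier, which the synopsis statistics entry calls *likely* and sections 3.9.4.3 and 3.11.4 call *possibly*.

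No new table of all-cause events is needed, since the protocol already lists them. The cost is one sentence, a few grid cells and a footnote. Reported adverse-reaction rates may be slightly higher. No dose or clinical rule changes.
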